### Qualitative methods

**
*i. Patient participants*
**

In up to 5 case sites we will carry out semi-structured, qualitative interviews with 40–50 patients and carers (~10 per case site), seeking to understand their views and experiences (also using interpreters where needed, to account for ethnic diversity). We will engage patients and carers who have taken part in VHGCs, as well as those who declined participation or were unable to attend sessions (e.g. due to digital exclusion). A subset of participants will be invited to follow-up interview 12 months later to reflect on longitudinal changes. Interviews will follow a flexible topic guide, will last 45–60mins, and will take place remotely (on the phone or video) or at participants’ homes, their GP practice or another preferred location.

To allow participants to collectively debate their views on VHGCs, we will conduct 4–6 focus groups, each involving 6–8 patients and carers (n=24–48) who have not already participated in interviews. Each group will last 60–80 minutes and will be led by an experienced moderator using a flexible topic guide. We will aim to align some of these focus groups with existing VHGC sessions (especially when these are designed to be short) to capture immediate thoughts and feedback patients might have on what has gone well or less well.

We will recruit patients across sociodemographic and ethnic backgrounds, health needs and conditions, and with different levels of self-assessed digital literacy/confidence. Groups with higher general practice consultation rates will be particularly targeted (asking each practice which groups tend to make most use of services locally), including those with long-term conditions, those with multi-morbidities, and people from underinvested communities.

**
*ii. Clinical and non-clinical NHS staff*
**

Recruitment will primarily focus on case sites, where we expect to engage at least 4–6 staff per site in semi-structured interviews (n=20–30 in total) to better understand VHGC delivery in the contact of broader organisational routines. This will include health professionals (GPs, trainees, practice nurses, healthcare assistants, pharmacists etc), practice managers, administrators, reception and IT staff. A subset of staff participants will be interviewed twice over 12 months, to be able to follow up on growing familiarity with VHGCs and any longer-term impacts on the service. Interviews will last 45 mins and will be carried out either in-person or on the phone/video. An indicative topic guide will be followed, tailored to different interviewees.

We will also carry out ethnographic observation focusing on back-end operational and technical processes required to run VHGCs, to enrol patients in VHGCs and support their participation (at least 2 visits per case site over 12 months). The team will observe 25 VHGCs (virtually or in-person) across the 5 case sites (~5 each), using video or audio recordings and field notes. Any documentation, VHGC materials developed by the practice, significant event details or other relevant, de-identified records will be retained for analysis.

**
*iii. National and local policy-makers and commissioners*
**

To further our understanding of evolving policy and guidance, national-level incentives and regulation, we will conduct semi-structured, elite interviews with 5–10 key national decision-makers (e.g. NHSE). At a local level we will interview 5–7 commissioners across the 5 case site localities and observe relevant meetings, to gain further insights on VHGC impact on service planning and access. Interviews will last 45mins and will be carried out in-person or on phone/video. Relevant policy reports, public-facing content and other relevant materials will be retained for analysis.

With informed consent (written or verbal), qualitative interviews, group discussions and a sample of VHGCs will be audio or video recorded, and professionally transcribed. Field notes will be taken during observation, and photos will be used to illustrate back-end operational processes. All data will be de-identified and uploaded to
NVivo 12 to support data management (
QualCoder is an open access alternative). Following data familiarisation and guided by our research questions, we will take an iterative approach to theory-informed, conceptual data coding in the first instance, following inductive, deductive and abductive approaches. We will compare and contrast data between cases, to develop an in-depth understanding of sociotechnical processes underpinning VHGC delivery and participation. Analysis will take place in parallel to data collection with a view to developing new theoretical insights. 

### Quantitative methods

**
*i. Description of VHGC delivery and resource use*
**

In each of the case sites we will collect descriptive data on the way VHGCs are delivered and the resources needed. These data will include the number and type of VHGC sessions, the number of patients participating in each VHGC and the number of patients invited to take part who choose not to participate. The data will be collected by the practice with support from the study team using structured proformas on a monthly basis. We will also collect key data, for those consultations observed by researchers, on timing and duration of VHGCs, resources needed (e.g. staff members) to deliver the sessions, and time and resources required to prepare for and follow up from each VHGC. The exact data required may depend on the way in which a practice chooses to deliver VHGCs but will likely include, the time at which the online session is started (e.g. by the ‘facilitator’), the time at which patients join the session, time spent facilitating technical issues, the time when the clinician joins the session (which in current VHGC models may be some time later than the patients), the time when the clinician leaves the session and the time when the session is ended. By examining this data we will gain an understanding of the time burden experienced by patients, GPs and other clinical and non-clinical staff, and how this changes over time.

**
*ii. Impact of VHGCs on patient experience, satisfaction and quality of life*
**

We aim to recruit up to 50 patients per practice who will consent to participate in a survey questionnaire comprising patient experience, satisfaction and healthcare-related outcome components, and to allow research access to their healthcare utilisation data. The survey will be administered online and offline, immediately following VHGC attendance (through a link shared on the same platform, e.g. Microsoft Teams, or in paper format for those attending in person), and will examine both patient experiences which relate directly to VHGCs (e.g. satisfaction with care received, inclusion and access implications, quality and safety of care, need for additional follow-up, travel time saved, time off work avoided etc.) as well as to wider experiences of healthcare in the practice (e.g. satisfaction with 1:1 care, perceptions on access, quality and safety). To develop the survey questionnaire, we will draw on questionnaires piloted in our previous research on patient experiences with video consultations and group clinics. We will also adopt or adapt items from existing surveys such as the GP Patient Survey (
https://gp-patient.co.uk/) and the Primary Care Outcomes Questionnaire (PCOQ)
^
31
^. We also expect new items to be developed. The findings will be used in descriptive analyses to provide a quantitative overview of patient experience of VHGCs.

In addition to the case sites, we will recruit an equal number of comparison practices where VHGCs are not being employed (matched with case sites on location, setting, size, deprivation, QOF). As with case sites, we will aim to recruit 50 patients from each comparison site with recruitment targeted at similar patients as those taking part in VHGCs in terms of age, gender and chronic conditions treated. They will receive a shorter version of the patient survey used in case sites with questions relating only to wider experiences of healthcare at their practice and will be asked to consent to research access to their healthcare utilisation data. Our team will also provide support to any comparison or case sites who choose to administer the Patient Activation Measure (PAM) in the context of local service improvement.

**
*iii. Impact of VHCGs on healthcare utilisation*
**

We will work with practices to collect data (using Word proformas) on patients’ primary care utilisation including the number, type (staff members involved, e.g. GP, nurse or other healthcare professional, and mode of consultation e.g., in-person, telephone, online) and duration of appointments. We will also obtain secondary care utilisation data from NHS Digital using Hospital Episode Statistics (HES) data. Comparisons will be made between patients at case and comparison sites in terms of number and duration of primary care consultations, number of A&E attendances, outpatient appointments (including numbers or proportion of eligible patients waiting more than six months), hospital admissions, unplanned hospital admissions and hospital admissions for ambulatory care sensitive conditions (conditions for which admissions could, in principle, be avoided by good primary care
^
32
^). Mixed effects models, with random intercepts for practice, will be used to analyse these data with the form of the model appropriate to the outcome (i.e. Poisson models for count of appointments/admissions and linear models for consultation durations). Adjustments will be made for patient factors including age, gender, deprivation, ethnicity and comorbidity status. Given the exploratory nature of this work we have not performed any formal power calculations and will interpret the results accordingly. Rather than focus on the presence or absence of statistically significant differences between groups, the analysis will instead examine confidence intervals as a guide to potential differences between the groups, to guide a larger, definitive study.

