Model inputs: the focus of the VHGC (e.g., diabetes annual reviews; peri and post menopause consultations) will be defined in consultation with case and comparison sites in WP3. A micro-costing analysis of VHGCs will be conducted in one of the five case sites in WP3 GP. Data on consultations (e.g. number and type of VHGCs) will be collected prospectively. The main source to estimate the unit cost of different types and modes of GP consultations will be the Unit Costs of Health and Social Care Manual (
https://www.pssru.ac.uk/unitcostsreport/). Over an up to 6-month period, all patients attending a GP consultation (any type and mode, but with the same focus as VHGCs) in one case and one comparison site will be invited to complete an online Measures of Health Benefit survey. This will include questions on utility-based health-related quality of life (i.e. EQ-5D-5L)
^
36
^, patient satisfaction (i.e. SOPS adaptation)
^
37
^ and personal details (e.g. age, weight, height).

Initial model inputs will be based on estimates of consultation costs, utility, and satisfaction. Given the limited data available to populate our decision model, and the need to make a number of expert-informed structural assumptions, we expect the results and conclusions derived from the early HEE to be subject to uncertainty. The impact of this on the decision uncertainty to consider VHGC a cost-effective addition to exiting models of GP healthcare provision will be explored using value of information analysis (VOI)
^
38
^. This methodology will enable us to identify the model parameters (and structural assumptions) considered to be the key drivers of decision uncertainty. Results from the VOI analysis will be used to inform the design of a future definitive study of a GP model of healthcare provision with VHGCs.

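### The utilisation contrast sets VHGC attenders against comparison patients with no stated attendance-based entry, so it is partly confounded by who attends

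*Protocol article*

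**What the plan says.** All of the following is in the Protocol article.

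- **Entry at case sites** (Quantitative methods, part ii). "We aim to recruit up to 50 patients per practice who will consent to participate in a survey questionnaire". The same consent covers access to utilisation data. On timing: "The survey will be administered online and offline, immediately following VHGC attendance".
- **Entry at comparison sites** (same part). "we will aim to recruit 50 patients from each comparison site with recruitment targeted at similar patients as those taking part in VHGCs". The similarity is defined as "similar patients as those taking part in VHGCs in terms of age, gender and chronic conditions treated". These practices do not run VHGCs and are "matched with case sites on location, setting, size, deprivation, QOF".
- **Contrast** (Quantitative methods, part iii, headed as impact on utilisation). "Comparisons will be made between patients at case and comparison sites in terms of number and duration of primary care consultations", together with hospital outcomes from HES. The models are mixed effects with a random intercept for practice. "Adjustments will be made for patient factors including age, gender, deprivation, ethnicity and comorbidity status". The work is called exploratory, no power calculation is made, and confidence intervals are to inform a larger study.
- **Non-attenders.** Part i counts those invited who do not take part. The Qualitative methods section interviews decliners and people unable to attend, with digital exclusion as an example. Neither group has a described place in the utilisation cohort.
- **Another frame in the same study** (Health economics evaluation, model inputs). The health-benefit survey invites "all patients attending a GP consultation (any type and mode, but with the same focus as VHGCs) in one case and one comparison site".

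**The concern.** Every case-site patient was invited, accepted and managed to join a session. A comparison patient needs the right age, gender and condition and must consent to the survey, but is not stated to have attended anything. People who would have declined a group, or could not have joined one, are therefore absent from the case cohort while their counterparts remain eligible in the comparison cohort.

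Willingness and ability to attend plausibly go with engagement, digital access and past use of services, all of which can affect later consultations and admissions. Practice matching balances practices, not who turns up within them. The named patient covariates do not measure these traits.

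At stake is the input to the next study. Confidence intervals describe sampling error. If the two groups differ systematically, an interval centred on the wrong value could mislead the planning of the definitive study about the size, or even the direction, of any effect.

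**Working it through.** The plan gives no power figure, effect size or uptake rate, so there is no stated figure to reproduce. The only design arithmetic is cohort size: 5 practices × 50 patients = at most 250 per group. The rest is illustration under assumed inputs.

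**Step 1. Which safeguards reach attendance?**

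| Safeguard in the plan | What it balances | Willingness or ability to attend? |
|---|---|---|
| Practice matching on five factors | Practices | No |
| Patient targeting | Age, gender, condition | No |
| Model adjustment, open list | Named: age, gender, deprivation, ethnicity, comorbidity | At most indirectly |
| Survey consent in both groups | Volunteering for research | Partly shared; attendance is not |

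**Step 2. Spurious rate ratio when VHGCs do nothing.** Let U be an unmeasured trait, standard normal among eligible patients. A fraction p attends; the latent attendance variable has correlation ρ with U. The utilisation rate changes by a factor R per SD of U. With b = ln R and c the standard normal quantile at 1 − p:

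rate in attenders ÷ rate in all eligible = Φ(bρ − c) / p

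Assumed, not from the documents: p 0.2 to 0.6, ρ 0.3 to 0.5, R 0.8 to 0.9.

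| p | ρ | R | bρ − c | Φ | Spurious rate ratio |
|---|---|---|---|---|---|
| 0.6 | 0.3 | 0.9 | 0.222 | 0.588 | 0.98 |
| 0.4 | 0.3 | 0.9 | −0.285 | 0.388 | 0.97 |
| 0.4 | 0.5 | 0.8 | −0.365 | 0.358 | 0.89 |
| 0.2 | 0.5 | 0.8 | −0.953 | 0.170 | 0.85 |

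Reversing the trait's effect reverses the bias. R = 1/0.9 in the first row gives 0.612/0.6 = 1.02; R = 1/0.8 in the last gives 0.233/0.2 = 1.16.

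**Step 3. A simpler cross-check.** If attenders use r times what non-attenders use, their rate relative to all eligible is r / (pr + 1 − p). With p = 0.4 assumed:

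- r = 0.9: 0.9/(0.36 + 0.6) = 0.94
- r = 0.8: 0.8/(0.32 + 0.6) = 0.87

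Both fall inside the range in step 2.

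**Step 4. Scale against the interval.** For 250 v 250 patients in 5 v 5 practices:

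Var(log rate ratio) = 2 × [(1/m + k)/250 + s²/5]

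Assumed: mean contacts m 5 to 8, overdispersion k 0.5, between-practice log-SD s 0 to 0.2.

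- Narrowest (m = 8, s = 0): variance 0.0050, half-width 1.96 × 0.0707 = 0.139, factor 1.15
- Widest (m = 5, s = 0.2): variance 0.0216, half-width 1.96 × 0.147 = 0.288, factor 1.33

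On the log scale the bias is 0.02 (ratio 0.98) to 0.16 (ratio 0.85). As a share of the half-width:

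- smallest bias, widest interval: 0.02/0.288 = 0.07
- largest bias, narrowest interval: 0.161/0.139 = 1.16

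So the bias can be negligible or about as large as the half-width.

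Both calculations treat comparison patients as an unselected sample of the eligible and take no account of covariate adjustment. To the extent that comparison volunteers resemble attenders, or the covariates pick up part of the trait, the bias would be smaller.

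**The case against.** The strongest reply is that this is an exploratory process evaluation. It declines to focus on significance, treats intervals as pointing to potential differences, and uses the survey findings descriptively. The practices are matched, and the covariate list is introduced as open, so prior utilisation could still be added. All of that is true and lowers the severity. It does not remove the problem: exploratory status excuses imprecision, not a systematic difference between groups, and an open list does not create a common entry event.

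Some stronger readings are tempting but unsupported:

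- **That comparison patients are balanced on age, gender and condition alone.** Practice matching and the model covariates go further.
- **That the plan wrongly omits start dates, follow-up windows, person-time or questionnaire order.** The article is silent on these, and a condensed article may leave them to the full protocol or analysis plan. Silence is not an error here.
- **That the bias is known to be large.** A reader taking only the lower end of step 3 could quote more than one standard error. That rests on an assumed uptake and an assumed difference in use, and the sign itself is unknown.
- **That the health economics survey already solves this.** It is only a partial precedent. It covers one case and one comparison site, and its case-site sample takes in consultations of any type, one-to-one included.

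**Conclusion.** The concern holds in limited form. As written, the plan compares people who attended a VHGC with people for whom no attendance-based entry is stated. Neither the practice matching nor the named covariates address willingness or ability to attend. The contrast headed as impact is therefore partly confounded by who attends, and its intervals do not show this.

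The size cannot be derived from the documents. Under the assumed inputs it runs from a spurious rate ratio of about 0.98 to about 0.85, and it would exceed 1 if attenders are the heavier users. The factual part, how each group enters, rests on the text; the magnitude rests on assumptions throughout.

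A reader might infer that the comparison is unusable or that the study must not proceed without a redesign. The documents do not support that, given the declared exploratory purpose. This is a should-fix, best settled before comparison recruitment starts, because analysis alone cannot repair the recruitment frame.

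**What to change.** 1. **Entry.** At each comparison practice, recruit patients after an attended one-to-one consultation with the same focus as the matched case site's VHGC, in the same calendar period.
2. **Index date.** Use the date of the recruiting contact in both groups: the VHGC session at case sites, the one-to-one consultation at comparison sites.
3. **Prior use.** Extract utilisation for a fixed pre-index period from the same practice records and HES, and add it to the model. The case sites already run VHGCs, so record any earlier attendance: for those patients the pre-index period is not free of exposure.
4. **Wording.** Describe the result as an association among attenders. Selection into the group format, through preference or digital access, remains after steps 1 to 3. The counts of invited non-participants already planned can be reported beside it.

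The cost is more than a change of wording. Comparison recruitment will move at the pace of routine appointments, and there is some extra data extraction. Recruiting at appointments may also over-represent frequent attenders, which the pre-index adjustment only partly addresses.

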### Study design

This mixed methods project includes three overlapping and interlinked work packages: A) Cross-sectional, UK-wide survey on group consulting provision over time (WP1), B) Co-design with patients and general practice staff with emphasis on inclusion and equity (WP2), C) Mixed methods, multi-site process evaluation in up to 5 case and 5 comparison sites (primarily GP practices in England) to generate actionable learning and in-depth understanding of implementation, from qualitative, quantitative and cost-related perspectives (WP3).

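### The only outpatient-waiting measure named is a six-month cut, which costs precision in a small comparison read through confidence intervals; the waiting time itself should be analysed as well where dates allow

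*Protocol article*

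**What the plan says.** The protocol article, under Quantitative methods, part iii (healthcare utilisation), lists the outcomes to be compared between patients at case and comparison sites. Waiting appears once, inside the outpatient item: "outpatient appointments (including numbers or proportion of eligible patients waiting more than six months". No waiting time, median wait or time-to-event analysis is mentioned, and no reason is given for choosing six months.

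On the analysis the article says "Mixed effects models, with random intercepts for practice, will be used to analyse these data", with the model suited to the outcome and two forms given: "Poisson models for count of appointments/admissions and linear models for consultation durations". Neither form is tied to a waiting proportion or a waiting time.

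On interpretation it says "Given the exploratory nature of this work we have not performed any formal power calculations", and that "the analysis will instead examine confidence intervals as a guide to potential differences between the groups, to guide a larger, definitive study".

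The sample is small. The Study design section describes a "multi-site process evaluation in up to 5 case and 5 comparison sites". For case sites the article says "We aim to recruit up to 50 patients per practice", and for the others "we will aim to recruit 50 patients from each comparison site".

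**The concern.** Before a patient can be classed as waiting more than six months, the wait must be known, or known to exceed that value. Keeping only the yes/no answer discards the rest. A change from five months to two, or from twelve to seven, would leave the measure unchanged. The same subsection keeps another duration, that of consultations, on its full scale, so the two are treated differently without explanation.

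This matters mainly because of how the results will be used. The plan disclaims power calculations and reads the comparisons through interval widths, which are meant to guide a later study. A choice that widens an interval weakens the product this analysis is meant to deliver.

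A smaller point concerns the choice between numbers and a proportion, which is left open. Recruitment at case sites has a ceiling of 50 per practice and may fall short, so a raw number of long waiters would move with recruitment and with how many patients are eligible. A proportion has a denominator and does not have that weakness.

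**Working it through.** There is no figure in the document to reproduce: no power, no waiting rates, no intraclass correlation. What can be checked is how much precision a cut costs under stated assumptions.

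**Inputs from the document.** At most 5 sites per group and 50 patients per site, so at most 5 × 50 = 250 patients per group. Practice enters as a random intercept.

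**Assumed inputs.** Share p waiting over six months: 10%, 20% or 30%. Log waits roughly normal and fully observed. Half of the patients eligible, so 125 per group, or m = 125 / 5 = 25 per practice. Intraclass correlation ρ of the wait within practice: 0.02 to 0.10.

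**Step 1: patient level.** With z the normal quantile that leaves p in the upper tail and φ the normal density, the relative efficiency of the cut is E = φ(z)² / [p(1 − p)], and the interval is 1/√E times as wide.

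| p | φ(z) | E | Width ratio |
|---|---|---|---|
| 10% | 0.1755 | 0.1755² / 0.09 = 0.34 | 1.71 |
| 20% | 0.2800 | 0.2800² / 0.16 = 0.49 | 1.43 |
| 30% | 0.3477 | 0.3477² / 0.21 = 0.58 | 1.32 |

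**Step 2: sensitivity to shape.** For exponential waits the efficiency is E = (ln p)² · p / (1 − p). This gives 0.59, 0.65 and 0.62 at p = 10%, 20% and 30%, and width ratios of 1.30, 1.24 and 1.27. The loss does not depend on the normal shape, but the 1.7 at p = 10% does.

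**Step 3: practice-level variation.** Clustering adds the same between-practice variance to both analyses, so it shrinks the ratio. To first order, the width ratio is √{[1/E + (m − 1)ρ] / [1 + (m − 1)ρ]}. With m = 25, (m − 1)ρ is 24 × 0.02 = 0.48 or 24 × 0.10 = 2.40.

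| p | 1/E | Ratio at ρ = 0.02 | Ratio at ρ = 0.10 |
|---|---|---|---|
| 10% | 2.92 | √(3.40 / 1.48) = 1.52 | √(5.32 / 3.40) = 1.25 |
| 20% | 2.04 | √(2.52 / 1.48) = 1.31 | √(4.44 / 3.40) = 1.14 |
| 30% | 1.74 | √(2.22 / 1.48) = 1.22 | √(4.14 / 3.40) = 1.10 |

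Replacing the first-order approximation by the exact intraclass correlation of the cut variable, under a bivariate normal model, moves these ratios by no more than about 0.02.

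**What the steps leave out.** They assume every wait is fully observed. Patients still waiting at data cut-off would be censored, which lowers the information in the full-scale analysis and so takes away part of the advantage.

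**The case against.** The strongest objection is to a reading that is tempting here: that the plan will compare waiting only as a six-month cut, and so widens its interval for no gain. The text does not support that. The six-month figure is introduced by open wording within the outpatient item, nothing rules out modelling the wait itself, and the article promises a model form suited to each outcome. An article may also leave the scale of a sub-measure, and the reason for a threshold, to a fuller document. This stands: the accurate statement is that the cut is the only waiting measure named.

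Nor is the cut pointless. The share of patients with long waits answers a service question that a shift in average waiting does not. This also stands, and is why the figure should be kept. It does not remove the case for adding the full scale, because an interval on waiting in general is what a later study would need and a cut estimates it poorly.

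A reader might also want to express the loss as power. That would rest on a shift the document never states, would vary with whether waits shorten or lengthen, and would not match a plan that sets significance aside. Interval width is the relevant measure.

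Two practical objections stand in part. The article says secondary care data come from Hospital Episode Statistics but does not say which dates will be held, and a wait known only to exceed six months is not a full-scale time. Restricting the analysis to referred patients could also introduce selection, since the care model may change who is referred. The addition should therefore depend on the dates being held and should use the plan's own eligible group.

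Finally, the stake is low: this is one part of one outcome in an openly exploratory comparison.

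**Conclusion.** The point holds as a modest improvement to the analysis. The article states nothing false here and does not contradict itself. It names one measure of outpatient waiting, a cut of a duration, in a comparison that is small and read through intervals. On assumed shares of 10% to 30% waiting over six months, that measure gives intervals about 1.3 to 1.7 times as wide as the full scale at patient level, and about 1.1 to 1.5 times with an assumed intraclass correlation of 0.02 to 0.10 and 25 eligible patients per practice. All of these rates, the shape of the waits and the correlation are assumptions, and censoring would bring the figures down further. The direction of the loss is secure; its size is not.

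**What to change.** In the healthcare utilisation subsection, add that where referral and appointment (or data cut-off) dates are held, the waiting time itself will also be analysed among the same eligible patients. Those still waiting would be censored at cut-off, and the model would carry the practice random effect and the covariates already listed. State who counts as eligible and from which date the wait runs. Keep the proportion waiting more than six months as a reported service figure with its denominator stated, and use it in place of raw numbers.

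The cost is one more model and a change of wording. The downsides are dependence on dates that the article does not confirm are available, including for patients not yet seen, and censoring that may remove part of the gain. If the dates cannot be had, say so and report the proportion alone.
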